# Protocol for a hybrid type 3 cluster randomized trial of a technical assistance system supporting coalitions and evidence-based drug prevention programs

**DOI:** 10.1186/s13012-021-01133-z

**Published:** 2021-06-25

**Keywords:** Community coalitions, Technical assistance, Interactive Systems Framework, Risk reduction behavior, Substance-related disorders, Prevention, Adolescent behavior, Implementation support, Sustainability

## Abstract

**Background:**

Over 5000 community anti-drug coalitions operating in the USA serve as a cornerstone of federal drug prevention. These coalitions, however, have demonstrated effectiveness in preventing substance use only when they use technical assistance (TA) and implement evidence-based programs (EBPs). The absence of TA and EBP implementation by coalitions is a key research-to-practice gap. The Coalition Check-Up TA system is designed to fill this gap by supporting community coalition implementation of EBPs. Existing TA models for evidence-based coalition approaches are resource intensive and coalition model specific. The Coalition Check-Up is a lower cost strategy that works with a variety of types of coalitions to support sustainable implementation of EBPs. This study protocol describes a hybrid type 3 effectiveness-implementation trial applying Wandersman’s Interactive Systems Framework to test the effects of the Coalition Check-Up on coalition EBP implementation capacity and outcomes. The Interactive Systems Framework outlines how the prevention support system—especially TA—bolsters EBP dissemination and implementation.

**Methods:**

Using a cluster randomized controlled design, this trial will test the overall effectiveness of the Coalition Check-Up, including how it contributes to EBP implementation and prevention of youth substance use. The first aim is to estimate the impact of the Coalition Check-Up on coalitions’ capacity to do their work. We will recruit 68 anti-drug coalitions for random assignment to the Coalition Check-Up or “TA as usual” condition. We will evaluate whether the Coalition Check-Up improves coalition capacity using measures of coalition member responses about team processes, coalition network composition, and collaborative structure. Our second aim is to estimate the impact of the Coalition Check-Up on implementation of EBPs, and our third aim is to estimate the impact of the Coalition Check-Up on youth substance use.

**Discussion:**

This project will clarify how the Coalition Check-Up, a scalable approach to TA due to its low cost, affects coalition capacity to support EBP implementation. Analyses also provide insight into causal pathways from the prevention support system to the prevention delivery system outlined by the Interactive Systems Framework. Results will build the evidence-base for how to support community coalitions’ sustainable implementation of evidence-based prevention programs and policies.

**Trial registration:**

Clinicaltrials.gov registration number NCT04592120. Registered on October 19, 2020.

Contributions to the literature
Community coalitions’ impact on public health hinges on their use of and sustainment of evidence-based programs. Yet little research investigates how to support such implementation.The Coalition Check-Up offers affordable technical assistance for coalitions’ use of evidence-based programs.This hybrid type 3 effectiveness-implementation trial tests Coalition Check-Up effects on evidence-based program implementation for drug prevention.The study is one of the first to test causal pathways outlined by the Interactive Systems Framework for Dissemination and Implementation.This study tests an innovation in the audit and feedback process—using motivational interviewing to support action planning based on feedback.

## Background

Several federal entities fund more than 5000 community anti-drug coalitions in the USA [1–3]. Such coalitions are attractive because they support community-driven solutions to local problems [4]. Community coalitions also promote processes that improve program implementation quality, including interorganizational collaboration, shared decision-making, and communication [5]. They can also support evidence-based practices (EBP) by serving as hubs of prevention expertise and support for the program delivery system—coordinating EBP selection, training, monitoring, evaluation, and problem-solving [5, 6]. For these reasons, coalitions provide potential key mechanisms for bridging the research-to-practice gap in substance use prevention.

### Technical assistance for community coalitions

Currently, there is insufficient knowledge about how to support coalitions’ EBP implementation. Community coalition models have demonstrated effectiveness only when they have entailed comprehensive TA and EBP implementation [7–10]. TA is particularly important for EBP implementation because EBPs require technical expertise, coaching, coordination among partners, and monitoring [11–13]. However, such TA often costs more than coalitions can afford. For instance, PROSPER and Communities That Care, two coalition-based approaches to prevention, have demonstrated effectiveness in implementing EBPs. Both entailed a 25% Full-Time-Equivalent TA provider per coalition [14, 15]. Budget-constrained TA providers often use group-based regional trainings and webinars that are not individualized or evidence-based [16]. Even individualized TA typically does not determine if coalitions are self-diagnosing correctly or addressing relevant capacities [17, 18]. Coalitions struggling to implement EBPs are often disconnected and do not reach out for help [19]. Currently, there is no evidence-based model for low or moderately intensive, sustainable TA.

As a TA model, the Coalition Check-Up requires 84% less TA time compared to the TA used in Communities That Care and PROSPER (4% FTE per coalition vs. 25% FTE). The Coalition Check-Up TA model is a low-intensity yet tailored solution to the tension between TA effectiveness and cost constraints. It is not specific to a particular community coalition model (e.g., PROSPER) or EBP, instead focusing on common dimensions of coalition capacity and program implementation intended to improve youth outcomes [20, 21]. Such a “light touch” intervention would be more easily sustained and is more likely to be adopted to support sustainability on a national scale than existing evidence-based TA models. Additionally, we do not yet know how coalitions can sustain implementation once TA diminishes. Although coalitions may continue to operate, their engagement and activities tend to decline when TA funding ends [22]. After TA loss, some coalitions have seen large declines in recruitment rates and implementation quality for prevention programming [22, 23]. One potential benefit of the Coalition Check-Up is preventing the usual loss of functioning among coalitions as they lose funding for TA. If effective, the Coalition Check-Up will provide lower-cost and thus more sustainable TA to help community coalitions implement EBPs.

### Coalition Check-Up conceptual framework

To help bridge these research-to-practice gaps, this study design applies the Interactive Systems Framework for Dissemination and Implementation. This framework focuses on how the prevention support system—especially TA—bolsters EBP dissemination and implementation. Figure 1 depicts how TA providers work with practitioners implementing EBPs in the prevention delivery system. Coalition Check-Up TA supports coalition capacity and EBP implementation, which are expected to subsequently contribute to reductions in youth substance use. Figure 1 illustrates aims 1–3 for testing these hypothesized paths of influence.

**Fig. 1 Fig1:**
[figure not shown]
Coalition Check-Up Conceptual Framework (adapted from Interactive Systems Framework)

Previous studies suggest that the coalition capacities shown in Fig. 1 are necessary to support EBP implementation [14, 21, 22, 24, 25]. Internal team processes such as group cohesion foster trust needed for sustained EBP implementation [22, 26–29]. Coalition network structure also influences coalition outcomes [25, 30]. For example, coalitions whose members seek advice outside their area of expertise have more support from community leaders and organizations, plus more detailed sustainability plans [30].

In Fig. 1, the 4-step Coalition Check-Up TA process provides proactive data-driven continuous quality improvement cycles that TA research suggests are particularly useful [17]. Step 1 in the Coalition Check-Up is assessing critical dimensions of the coalition’s capacity and EBP implementation. A coalition profile based on assessment data is reviewed in Coalition Check-Up step 2. Here the TA provider works with the coalition to consider several dimensions of coalition capacity and EBP implementation while celebrating strengths and prioritizing areas for growth. Once areas for growth are prioritized, the TA provider uses structured action planning in step 3 to help coalition members establish consensus on how to improve each. For example, the Coalition Check-Up may identify network structural characteristics such as centralization of influence and information as problematic [31]. The TA provider can then help a coalition develop an action plan to share decision-making power more broadly. To support step 3, TA providers draw upon a user-friendly guidebook, based on a comprehensive review of research for improving each dimension of coalition capacity and EBP implementation in the Coalition Check-Up assessment. This guidebook replaces otherwise improvised planning efforts and can speed decision making, thus reducing TA and coalition burden in creating action plans. In step 4, TA providers review and support progress on action plan implementation with the coalition. Efforts are evaluated every year after the initial assessment in a continuous quality improvement cycle.

Central to the Coalition Check-Up is its use of an “audit and feedback” implementation strategy, whereby performance data is collected and reviewed to inform continued improvement [32]. Following recommendations from the audit and feedback literature, the Coalition Check-Up identifies and addresses coalition and EBP implementation capacity deficiencies that frequently lead to failure [33]. A key innovation of the Coalition Check-Up is its use of motivational interviewing to support action planning and implementation based on an audit and feedback. TA providers use motivational interviewing techniques to cultivate a coalition-driven change process. By clarifying the benefits of change and addressing barriers without imposing recommendations, TA providers can guide coalitions to embrace change. These processes strengthen coalition motivation to develop and execute their own action plans [34].

We have found that without the structured Coalition Check-Up action planning process, coalitions do not typically use assessment reports or ask for help in doing so. For example, when a technical assistance provider faced budget cuts, they made face-to-face meetings to discuss evaluation data available only on request; only a small percentage (approximately 15%) of coalitions pursued them [35]. Thus, the Coalition Check-Up assessment with TA process appears to be critical for proactively promoting both motivation and capacity to use the data to make decisions about next steps, thereby improving EBP implementation quality [36].

Limited use of feedback for improvement purposes is a key challenge for audit and feedback as an implementation strategy [33]. Evidence suggests that audit and feedback interventions yield only modest improvements in practice [37]. To test the potential of more proactive TA to actualize benefits of audit and feedback, the current study compares coalitions receiving a rudimentary audit and feedback process (“TA as usual”), to those receiving the same audit and feedback materials combined with brief TA outreach that employs motivational interviewing to support action planning and action plan implementation. Specifically, we test the moderating influence of two core processes thought to strengthen audit and feedback: (1) fidelity to motivational interviewing techniques and (2) the collaborative working relationship between the person providing feedback and the coalition. We also test two factors thought to mediate the influence of audit and feedback on outcomes: (1) action plan quality and (2) action plan implementation [38].

### Objectives and aims

The testing of audit and feedback processes occurs as part of our larger main objective, which is to test the overall effectiveness of the Coalition Check-Up, including how it contributes to EBP implementation and prevention of youth substance use. Building on the Interactive System Framework, our central hypothesis is that the Coalition Check-Up enhances communities’ prevention support systems, thereby increasing coalition capacity for EBP implementation and the probability that EBPs will reduce youth substance use. This research will build the evidence-base for a scalable TA model, indicating how to intervene with community coalitions to maximize EBP fidelity and sustainability. To achieve our objectives, we will test this central hypothesis by pursuing three specific aims:

#### Aim 1

Estimate the impact of the Coalition Check-Up on coalition capacity. Coalitions will be randomly assigned to the Coalition Check-Up or “TA as usual” condition. We will evaluate whether the Coalition Check-Up improves coalition capacity using measures based on coalition member reports of team processes, network composition, and collaborative structure.

#### Aim 2

Estimate the impact of the Coalition Check-Up on implementation of evidence-based programs. We will test the hypothesis that coalitions receiving the Coalition Check-Up will implement EBPs with greater: (a) quantity, (b) quality, and (c) sustainability. We will also test coalition capacity as a mediator of Coalition Check-Up impact on EBP implementation.

#### Aim 3

Estimate the impact of the Coalition Check-Up on youth substance use. We will test the hypothesis that communities participating in the Coalition Check-Up will reduce youth substance use, including alcohol, tobacco, marijuana, and opioids, relative to communities whose coalitions receive TA as usual. We will also test EBP implementation as a mediator of the Coalition Check-Up impact on youth substance use.

## Method

This study is classified as a hybrid type 3 effectiveness-implementation trial, given its focus on testing a strategy for supporting EBP implementation, while still examining youth outcomes [39]. In this parallel groups cluster randomized trial, we will randomly assign existing Pennsylvania and Missouri anti-drug community coalitions to either the Coalition Check-Up or a comparison condition. Both study arms will have access to TA as usual, including regional trainings and TA by phone. As illustrated in the Fig. 2 CONSORT diagram, all community coalitions in the study will participate in the same annual assessment process and receive a report that summarizes the data collected. However, only coalitions assigned to the Coalition Check-Up will receive personalized outreach by TA providers. This creates a robust comparison because of the prior evidence that coalitions are unlikely to make effective use of the feedback reports without personalized TA.

**Fig. 2 Fig2:**
[figure not shown]
CONSORT diagram

### Coalition recruitment

We will recruit 68 coalitions from community anti-drug coalitions across Pennsylvania and Missouri, USA. This coalition population is similar to other US coalitions, which enhances study generalizability. These coalitions have received funding from a wide variety of sources, and their activity levels have fluctuated with changes in funding levels over time. Coalitions function in rural, suburban, and urban areas, ranging in age from 1 to 30 years old. We connect with these coalitions through the Evidence-based Prevention and Intervention Support (EPIS) group in the Pennsylvania State University’s Prevention Research Center. The EPIS team interfaces with community agencies, schools, and coalitions to provide support to those attempting to integrate prevention research into their practices.

We are using a layered targeted strategy to recruit coalitions, first with email communications from EPIS TA staff. We then introduce the project at coalition regional meetings organized by EPIS, providing time for questions and small group discussion to connect project researchers with coalition members. We then conduct follow-up phone calls and online meetings. The decision to participate rests on each coalition’s leadership team or at times with the full coalition.

#### Inclusion criteria

To be eligible, coalitions must (1) have been in existence for at least 1 year, (2) have a designated coordinator, (3) have at least quarterly meetings in which multiple sectors of the community attend, (4) currently support implementation of drug prevention activities or secured funding to do so, (5) be willing to complete coalition capacity and EBP implementation assessments annually, and (6) be willing to participate in four in-person meetings annually with the Coalition Check-Up TA provider.

### Randomization

Matched pairs of coalitions will be randomly assigned to the Coalition Check-Up condition or TA as usual. Coalitions will be matched on level of TA availability at baseline (0 = none, 1 = occasional trainings and group TA, 2 = regularly scheduled group TA, 3 = group TA and regularly scheduled one-on-one supervision, 4 = regularly scheduled one-on-one capacity-building TA), years in operation, coalition model employed, population density, US Census poverty rate, and availability of funding. A random number seed will be generated by an external third party using random.org. SAS Proc Surveyselect uses this random number seed to select one of each pair of coalitions recruited into the study as the intervention condition. Data collectors and data analysts will be blind to study condition, with no circumstances under which unblinding is permissible.

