### Power analysis

We used Optimal Design to estimate power for cluster-randomized trials [60]. In this study, youth-level substance use data and program-level implementation data are clustered within coalitions, which is the level of random assignment. Overall, we will have a power of .80 to detect Cohen’s *d* effect size ranges as follows: aim 1, .24 to .37, a small to medium effect, depending on the measure of coalition capacity; aim 2, .31 to .42, a medium effect, depending on the EBP implementation measure; and aim 3, .25, a small effect, for measures of youth substance use.

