### Data analytic plan

For aim 1, multi-level longitudinal growth models will be used to test our hypotheses that coalitions assigned to the Coalition Check-Up condition will show improving coalition capacity over time compared to the comparison condition. Our first step entails testing for baseline differences on all measures of coalition capacity between the two experimental conditions. All models will be estimated in MPlus using full information maximum likehood, which has the advantage of being able to estimate missing data [61].

We will model coalition structural characteristics (decentralization, multiplexity, sectoral diversity, intersectoral communication) as coalition-level dependent variables for aim 1. These dependent variables will be predicted by the experimental condition (0=control; 1= Coalition Check-Up), controlling for potential confounders (e.g., coalition model). Once we have multiple waves of data, measurement occasion will be repeated within coalition, and we will utilize growth modeling in our tests of Coalition Check-Up impact on coalition capacity. We will include pretest (i.e., year 0) measures in the model, enabling us to examine change in these characteristics over time between the two groups. Analyses will start by testing unconditional longitudinal models with maximum likelihood estimation in order to find the best functional form, after which we will test our hypotheses [62]. We will identify the trajectory of coalition capacity using model fit indices—including the AIC, BIC, and the −2 Log Likelihood deviance across different types of longitudinal models, including (a) the empty model (i.e., model with only a random intercept), (b) polynomial growth models, (c) polynomial growth models with random slopes, and (d) piecewise models [13, 62]. Once the developmental trajectory of coalition capacity is properly modeled, it will be predicted by experimental condition (0=control; 1= Coalition Check-Up), controlling for potential confounders.

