#### Aim 3: Analyses

The final aim will be to test the hypothesis that communities receiving the Coalition Check-Up will reduce youth substance use relative to communities in the “TA-as-usual” condition. Youth reports of substance use will be nested in school district (i.e., community or coalition level) via multilevel models. We will start by testing for differences in baseline levels of youth substance use between the two experimental conditions, to examine balance after randomization. If these comparisons identify a difference between the two conditions on a particular measure, it will be included as a covariate in the modeling. Then, youth substance use outcomes in year 3 will be predicted by experimental condition. A longer-term analysis of the Coalition Check-Up’s impact on youth substance use becomes possible with year 5 outcome data. These longer term outcomes will capture the effect of the Coalition Check-Up delivered as a continuous quality improvement cycle over years 2–4 of the study. We will use the same analytic models in year 5 as year 3, given that the data is identifiable at the school-district level but not the student-level.

We will examine 8 youth substance use outcomes (see the “Aim 3: Measures—youth substance use” section) in two multivariate multi-level models [62]. The first model will test past 30-day use of alcohol, tobacco, marijuana, and opioids simultaneously within the coalition’s catchment area [62]. The second model will test lifetime usage outcomes of the same substances. If an overall significant effect is found for the Coalition Check-Up in a particular multivariate model, follow-up tests will examine the specific substances as separate dependent variables [62]. These models extend analyses of Pennsylvania Youth Survey data conducted by [name] and [name] by taking advantage of increased levels of survey participation, the availability of community-level pretest measures of youth substance use, and the collection of detailed EBP implementation data [24, 59, 65].

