### Limitations

A potential challenge of this project is keeping the coalitions engaged in the Coalition Check-Up and focused on the development and implementation of action plans addressing prioritized areas for growth. Success in this regard may depend on a strong relationship between the TA provider and the coalition, which we include in our fidelity monitoring protocol. TA use of motivational interviewing should help in promoting a strong relationship and in encouraging coalitions to implement their action plans [72].

Another problem could be lower than expected participation in Pennsylvania Youth Survey or the Missouri Student Survey. If we identify school districts in participating communities without student data, a new data collection incentive plan will provide financial incentive for missing school districts to participate in data collection. We will discuss with the state-level survey sponsors to see what logistical support we can offer schools in missing districts.

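### Coalitions are randomised within matched pairs, but the models described for Aims 1 to 3 use neither the pair nor the full set of matching factors, which gives up precision

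*Protocol article*

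**What the plan says.** Randomization (protocol article): "Matched pairs of coalitions will be randomly assigned to the Coalition Check-Up condition or TA as usual". The six matching factors are technical-assistance availability, years in operation, coalition model, population density, poverty rate and availability of funding. The software is to "select one of each pair of coalitions recruited into the study as the intervention condition". Coalition recruitment gives the number: "We will recruit 68 coalitions from community anti-drug coalitions across Pennsylvania and Missouri, USA", which makes 68/2 = 34 pairs.

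The analysis sections then describe the models aim by aim:
- **Aim 1, structural characteristics:** "These dependent variables will be predicted by the experimental condition (0=control; 1= Coalition Check-Up), controlling for potential confounders (e.g., coalition model". Coalition model is the only matching factor named, and only as an example.
- **Aim 1, team processes:** members nested in coalitions, with condition at coalition level.
- **Aim 2:** the named covariates are all at program level (type, complexity and, for sustainability planning, baseline longevity).
- **Aim 3:** a baseline youth measure enters only if the arms are found to differ on it. On nesting: "Youth reports of substance use will be nested in school district (i.e., community or coalition level) via multilevel models".

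No pair term appears in any of them. The Power analysis section says that "youth-level substance use data and program-level implementation data are clustered within coalitions, which is the level of random assignment".

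**The concern.** Matching is done so that coalitions in the same pair resemble each other on things that predict the outcome. When it works, the arm difference varies less than it would between two independent groups of 34. A model without the pair, or without the factors that defined it, leaves that shared variance in the error term. The standard error is then too large, the test is conservative, and the trial has less power than its design can deliver. With 34 coalitions per arm, power is scarce.

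A smaller point concerns Aim 3. The article treats school district and coalition as one level without showing that they correspond one to one. If some coalitions cover several districts and only a district random effect is fitted, the error runs the other way.

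**Working it through.** **Inputs from the article:** 68 coalitions, one of each pair to intervention, power .80, Aim 3 detectable d = .25.

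**Assumed, because the article does not give them:** two-sided alpha 0.05; intraclass correlation ρ; youth per coalition n; residual within-pair correlation r; districts per coalition m; share s of district-mean variance common to a coalition.

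**1. The plan's own figure.** "Overall, we will have a power of .80 to detect Cohen’s" d of .25 for Aim 3. The usual two-level formula is MDES = M × √(4[ρ + (1−ρ)/n]/J), with J = 68 and M = 2.843 (noncentral t, 66 df). Solving for d = .25:

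ρ + (1−ρ)/n = .25² × 68 / (4 × 2.843²) = 0.131.

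That implies ρ of about .12 to .13 for n = 100 to 1,000. Since ρ, n and any covariate R² are not given, the figure can be neither confirmed nor refuted, and nothing below depends on it being wrong.

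**2. Detectable effect with and without pairs.** Take one value per coalition and an unadjusted comparison, in coalition-level SD units.
- Unpaired, 66 df: 2.843 × √(4/68) = 0.69.
- Paired, 33 df, M = 2.886: 2.886 × √(4/68) × √(1−r) = 0.70 × √(1−r).

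**3. True alpha of the unpaired test.** Its standard error is too large by 1/√(1−r), so alpha = 2[1 − Φ(1.96/√(1−r))].

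**4. Power of the unpaired test where the paired test has 80%.** Approximately Φ(2.886 − 1.997/√(1−r)), where 1.997 is the critical t on 66 df. For r = 0.2 this is Φ(2.886 − 2.232) = Φ(0.654) = 74%.

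| r (assumed) | Paired MDES | True alpha, unpaired | Power, unpaired |
|---|---|---|---|
| 0.2 | 0.63 | 2.8% | 74% |
| 0.3 | 0.59 | 1.9% | 69% |
| 0.5 | 0.50 | 0.6% | 52% |

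Simulating 50,000 trials per value gave unpaired type I error of 4.9%, 2.9% and 0.6% at r = 0, 0.2 and 0.5. The paired test stayed between 4.8% and 4.9%.

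**5. Break-even and worst case.** Pairing costs degrees of freedom. It pays once r exceeds 1 − (2.843/2.886)², about 0.03. At r = 0 with fixed pair effects, the detectable effect grows by 2.886/2.843 = 1.015, that is 1.5% (0.69 to 0.70).

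**6. On the Aim 3 scale.** If .25 is the unpaired figure, the paired one is .25 × 1.015 × √(1−r): .254 at r = 0, .241 at 0.1, .227 at 0.2 and .180 at 0.5.

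**7. District clustering, conditional only.** The ratio of true to model standard error is √(1 + (m−1)s).
- m = 1, the article's own equation of the two levels: ratio 1.00, type I error 5%.
- m = 2, s = .25: √1.25 = 1.12, type I error 8%.
- m = 3, s = 1: √3 = 1.73, type I error 26%.

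Neither m nor s is in the article.

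**The case against.** **The article is condensed and no analysis plan is shown.** A pair term or a final covariate list could well be there. The Aim 1 allowance for confounders, whose one example is itself a matching factor, leaves room for this fix. That stands to the extent that the criticism must be confined to the models as described. But the description is detailed: it gives nesting levels, random intercepts, covariates and the level at which condition enters. It even says which regression needs no adjustment for nesting. Across all three aims, what it sets out is an unpaired analysis of a paired design.

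**The figures are not for the planned models.** This also stands. They describe a single unadjusted comparison, while the plan uses growth models with pretest measures in Aims 1 and 2. Those may take up much of the variance that matching addresses, so the residual r, and with it the gain, may be smaller.

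**Stronger readings the article does not support:**
- A reader might infer that ignoring the pairs threatens validity. It does not: type I error stays at or below nominal.
- A reader might set the 0.69 above against the stated detectable effects of .24 to .42 and call those wrong. Their inputs are not given, so that does not follow.
- A reader might infer that Aim 3 clusters by district in place of the randomised coalition and so inflates false positives. The Aim 3 sentence equates district with coalition level, and the Power analysis section names the coalition as the cluster. The phrase "If we identify school districts in participating communities without student data" has both nouns plural and fits one district per community. Missouri's county counts describe statewide survey participation and say nothing about coalition boundaries. Only the lack of a shown one-to-one match remains.

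**Conclusion.** The point holds as a loss of efficiency. As described, the models for Aims 1 to 3 use neither the 34 pairs nor the full set of six matching factors, so they discard whatever precision the matching provides. Under the assumed correlations, the loss is 6 to 28 percentage points of power (80% against 74% to 52%). It is close to nothing if the residual correlation is near the break-even of 0.03. The article gives no information on where in that range the trial lies.

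The Aim 3 nesting is a request for clarification, not an error: the inflation in step 7 arises only if coalitions span several districts and no coalition level is fitted. The change is worth making because the likely gain clearly exceeds its cost.

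**What to change.** 1. Add a random pair intercept to every outcome model in Aims 1 to 3, so that a pair that loses one coalition still contributes. Alternatively, prespecify all six matching variables as coalition-level covariates in place of the open-ended reference to confounders.
2. In Aim 3, state that the coalition is the cluster level at which condition and its degrees of freedom sit, with districts nested within it where a coalition covers more than one. Where each coalition has one district, this reduces to the model already described.

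Both are changes of analysis wording, with no effect on recruitment or data collection. The statistical cost of the first is at most about the 1.5% in step 5, if pairs are fitted as fixed effects and the matching turns out to be uninformative.
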